### Interventions

All patients in both groups will undergo zone-5 flexor tendon repair using the four-stranded modified Kessler technique, interrupted epineural nerve repair, and anastomosis of the principal artery.

## Procedure

### Preoperative management

The Department of Hand Surgery proforma will be used to gather baseline demographic data, which will be used to screen patients for inclusion and exclusion criteria. A preoperative clinical assessment will assess several factors that may impact the patient’s outcome following surgery. A radiograph of the affected extremity will be taken to rule out fractures. All patients will get preoperative antibiotics with tetanus prophylaxis to prevent infections. Every patient will have routine operational investigations, such as complete blood counts and serology testing, in accordance with hospital and departmental policy. Following a clear and concise explanation of the trial, written informed permission will be obtained from the participants.

### Surgical procedures

All patients will undergo surgery under regional or general anesthesia and a tourniquet. All the repair procedures will be done under loupe or microscope magnification. Structures will be repaired in the serial order of deep to superficial and far corner to near. Flexor tendons will be repaired using a modified Kessler repair involving four-strand core sutures using 3 − 0 polypropylene with the knot at the cut end. 8 − 0 or 9 − 0 nylon is used to repair the median/ ulnar nerves and radial/ulnar arteries.

### Follow-up

Patients in both groups will be followed up each at six weeks, three, six, and 12 months.

### Outcomes

Primary outcome and Secondary outcomes.

Patient-related variables:

Age.Gender.Co-morbidities.Personal habits.Preoperative mobility.Patient injury data will be sub-grouped based on the classification of Koshy et al. They will be divided into three grades based on the lacerated structures, laceration type, and repair type [3].

Primary outcome: Tang’s criteria (Total active movement) [17].

Secondary outcome:

Independent FDS function.Sensory assessment.Pinch strength.Grip strength.MCHQ (Michigan Hand Outcome Questionnaire) [18]– Functional outcome.To look for causes of motor passivity that could influence the outcome, we propose using the Kinesiophobia Causes Scale (KCS). It is observed that fear of movement, considered to be a part of an individual’s personality, could be a major limitation to motor activity. This type of behavior is described as kinesiophobia and can be documented using this scale [19].

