### Sample **size calculations**

At a 5% level of significance with 80% power and an effect size of 0.3, the minimum sample size (per group) required for a two-group repeated measures study design involving one primary quantitative outcome measured across four time points [six weeks, three months, six months, one year] (correlation among repeated measures is clinically presumed to be 0.3), was 44, i.e., 22 per group.

The sample size is computed using G*Power 3.1.9 and based on the formula mentioned below.

Formula.

$$n=\frac{2}{{{\delta ^2}}}\left[ {\mathop \sigma \nolimits_{b}^{2} +\frac{{{\sigma ^2}}}{k}\left[ {1+\left({k - 1} \right)\rho } \right]} \right]{\left({{z_{{\raise0.7ex\hbox{$\alpha $} \!\mathord{\left/ {\vphantom {\alpha 2}}\right.\kern-0pt}\!\lower0.7ex\hbox{$2$}}}}+{z_\beta }} \right)^2}$$

Where,

$$\mathop \sigma \nolimits_{b}^{2} $$: Between group variance

$${\sigma ^2}$$: Within group variance

$$\rho $$: Intra class correlation coefficient

$$\delta $$: Effect size

*K*: Number of repeated measures

$$\alpha $$: Significance level

$$1 - \beta $$: Power

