### Statistical **analysis**

An MS Excel spreadsheet application will code and record the data. Programming or SPSS v23 will be utilized to analyze the data. For continuous variables, descriptive statistics will be explained as means/standard deviations, IQR/ medians, and percentages/ frequencies; categorical variables will take the form of a chi-square test.

Where applicable for data visualization, data will be displayed graphically using pie or bar charts for categorical data and box-and-whisker plots, histograms, and column charts for continuous data. The independent sample “t” test will be utilized for group comparisons for continuously distributed data, and repeated measures ANOVA (Analysis of Variance) will be employed to evaluate the results across time and among the groups.

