## Discussion

The proposed novel study of a double-blind, randomized trial conducted at a single center, comparing the functional results of early active motion therapy with passive mobilization in zone-5 flexor tendon injuries, is unique and has not been described earlier. It will answer the role and possible benefits of a more aggressive early active mobilization program. Additionally, the study will give information on patient-reported outcomes and address the incidence of complications.

How successfully a flexor tendon heals depends on several factors, including the type of injury, any concurrent nerve damage, the surgeon’s experience, treatment methods, and postoperative care [2, 8, 9, 20]. Several different postoperative mobilization techniques exist, from rigid immobilization to early, protected finger movement. However, the description of the rehabilitation program after flexor tendon surgery in zone-5 is not well documented in the literature [21]. The only regime followed for injury in these regimes was a form of early protected passive range movements. The majority of the studies reported acceptable function with early mobilization, with a higher complication rate being observed in more severe tendon and nerve injuries [2, 10, 22–24].

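### Injury grade is recorded on every patient and could be added to the primary model at almost no cost; this is a free gain in precision, not the correction of an error

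*Protocol article*

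**What the plan says.** - **Eligibility and recording.** Grades 1, 2 and 3 of the spaghetti-wrist classification are all eligible (Inclusion criteria). Under Outcomes, injury grade is listed with the patient-related variables: "They will be divided into three grades based on the lacerated structures, laceration type, and repair type".
- **Prognosis.** The Discussion states: "How successfully a flexor tendon heals depends on several factors, including the type of injury, any concurrent nerve damage". It also summarises earlier studies as reporting acceptable function after early mobilisation, "with a higher complication rate being observed in more severe tendon and nerve injuries".
- **Allocation.** Randomization and blinding describes 1:1 block randomisation, 22 per arm, done 24 hours before surgery. No stratification factor is named.
- **Analysis.** Statistical analysis names an independent-sample t "test will be utilized for group comparisons for continuously distributed data" and a repeated measures ANOVA over time and between groups. No covariate appears with either.
- **Size.** The trial is sized for "one primary quantitative outcome measured across four time points". The inputs are "At a 5% level of significance with 80% power and an effect size of 0.3" and "correlation among repeated measures is clinically presumed to be 0.3", and the result "was 44, i.e., 22 per group".

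**The concern.** The article names a feature of the injury that it believes affects recovery and collects a three-level summary of that feature on everyone. It then describes neither an allocation nor an analysis that uses the summary in the treatment comparison. Two things are given up.

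First, whatever part of the spread in TAM is explained by grade stays in the error term, so the confidence interval is wider than it needs to be. Second, with 22 patients per arm and no stated stratification, the grade mix can differ visibly between arms. An adjustment added only after such a difference is seen would look chosen for its result; one fixed in advance would not.

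**Working it through.** **1. Reproduce the plan's figure.** Inputs, all from Sample size calculations: alpha 0.05, f = 0.3, m = 4 measurements, rho = 0.3, N = 44. The value 0.3 has to be read as Cohen's f (d = 0.6 on a single measurement) for 44 to come out. The between-groups test in a repeated measures ANOVA has

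lambda = N f² m / (1 + (m − 1) rho) = 44 × 0.09 × 4 / 1.9 = 8.34, with 1 and 42 degrees of freedom.

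Power from the noncentral F distribution is 0.805. At N = 42 it is 0.786, so 44 is the smallest even total that reaches 80%. The stated figure reproduces, and it contains no covariate.

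**2. Power with grade in the model.** A three-level factor takes 2 degrees of freedom (42 − 2 = 40). If grade explains a share R² of the within-arm variance of the patient mean, lambda becomes 8.34 / (1 − R²). R² is not in the document and is assumed. The small loss when grade is not perfectly balanced between arms is ignored.

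| Assumed R² | lambda | Power, N = 44 |
|---|---|---|
| not adjusted | 8.34 | 0.805 |
| 0 | 8.34 | 0.804 |
| 0.10 | 9.26 | 0.844 |
| 0.20 | 10.42 | 0.883 |
| 0.30 | 11.91 | 0.920 |

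The standard error shrinks by a factor √(1 − R²): 0.95, 0.89 and 0.84 for R² of 0.10, 0.20 and 0.30.

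**3. How often grade mix differs by chance.** The prevalence p of a given grade is also not in the document. Treat the counts in the two arms as independent Binomial(22, p). A gap of 5 patients is 5/22 = 23 percentage points.

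| Assumed p | P(arms differ by 5 or more) |
|---|---|
| 0.20 | 0.09 |
| 0.33 | 0.15 |
| 0.50 | 0.17 |

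Fixing the total with the grade and splitting it at random gives similar values: 0.16 for 11 of 44, 0.20 for 15 of 44 and 0.13 for 22 of 44. (With 22 of 44 the gap is always even, so 5 or more means 6 or more.)

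**4. What such a gap does to the estimate.** Take one grade against the rest, p = 1/3 and R² = 0.10. The grade effect is √(0.10 / (1/3 × 2/3)) = 0.67 SD of the patient mean. A gap of 5 patients moves the group difference by 0.227 × 0.67 = 0.15 SD. The standard error of the difference is √(2/22) = 0.30 SD, so the shift is about half a standard error. The planned effect on the same scale is 0.6 / √(1.9/4) = 0.87 SD, so the shift is about 17% of it. That is noticeable but not decisive.

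**The case against.** The strongest reply is that nothing here is wrong. Under randomisation the unadjusted comparison is unbiased and keeps its type I error, and chance imbalance is already counted in its standard error. The trial reaches its stated 80% without adjustment. The Statistical analysis section is a short list in a condensed article; it never says unadjusted, and a covariate list is commonly left to the analysis plan, which is not shown. All of this stands, and it is why the point is an improvement and not a fault.

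The evidence on prognosis is also looser than one would like. The severity remark concerns complications, not TAM. The remark on healing is general to flexor tendons, lists other influences too, and does not mention the three grades. No relation between grade and TAM is given, so the gain may be close to nil.

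Grade depends partly on the type of repair, and randomisation precedes surgery by 24 hours, so grade may be settled only after allocation. This affects how the covariate should be recorded, and it makes stratifying by grade harder.

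Two stronger readings are tempting and not supported. A reader might infer that a grade imbalance would bias the trial or be mistaken for a treatment effect; the valid type I error and the half-standard-error shift above do not bear that out. A reader might also infer from the mention of sub-grouping that treatment will be compared within grades, at about 7 patients per arm and grade. The Outcomes section only classifies injuries there, and no within-grade comparison is planned.

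**Conclusion.** The point holds as an optional improvement. The named analysis is valid and adequately powered on its own terms (0.805). Adding grade loses 0.001 of power if grade is not prognostic and gains about 0.04, 0.08 or 0.12 if it explains 10, 20 or 30% of the variance in patient-mean TAM. It also removes the effect of a grade imbalance of 5 or more patients, which would arise in about 9% to 17% of trials for a prevalence between 20% and 50%. R² and prevalence are both assumptions; the documents fix neither. The figures further assume that TAM is analysed as a quantitative outcome, as in the sample size section, and that grade is recorded without knowledge of allocation.

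**What to change.** In Statistical analysis, state that the repeated measures model for TAM includes injury grade (1/2/3) as a pre-specified three-level fixed factor, and that the models for the continuous secondary outcomes do the same. Name the grade-adjusted group difference as the primary estimate and the unadjusted difference as supportive.

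Add that grade is assigned from the injury findings, by staff blinded to allocation, before rehabilitation starts on day 5, so that it cannot be influenced by the assigned regime.

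The cost is two degrees of freedom and one line of text, with no new data and no change in sample size. The change should be made before any unblinded look at outcomes. If a separate analysis plan already adjusts for grade, the article's section need only be aligned with it.

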**Exclusion criteria**:

Associated hand/ wrist fractures.The active movement of the digit is preserved at IP joints (Only one flexor tendon for finger or partial injury not requiring four-strand Kessler repair).Polytrauma.Patient unable to attend hand therapy program.

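### Grip and pinch strength are compared with no covariate; measuring the opposite hand once at enrolment would be a cheap gain in precision

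*Protocol article*

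**What the plan says.** - **Outcomes.** Grip and pinch are secondary outcomes, in the list "Independent FDS function.Sensory assessment.Pinch strength.Grip strength". Their scale is not stated.
- **Outcomes, patient-related variables.** After age and gender the list continues "Co-morbidities.Personal habits.Preoperative mobility", followed by injury grade. Preoperative mobility is its only functional item, and it is not called a baseline or a covariate.
- **Exclusion criteria.** Patients are excluded if "The active movement of the digit is preserved at IP joints".
- **Follow-up.** Assessments are at six weeks and three, six and 12 months. No outcome assessment before surgery is listed.
- **Statistical analysis.** A t test is planned ("test will be utilized for group comparisons for continuously distributed data"), with repeated measures ANOVA for results over time and between groups. No covariate is named.
- **Sample size calculations.** The calculation is made "At a 5% level of significance with 80% power and an effect size of 0.3", for "one primary quantitative outcome measured across four time points", with a correlation of 0.3 between visits. It gives 22 per group.

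Neither the opposite hand nor hand dominance appears in the article.

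**The concern.** Grip and pinch strength differ between adults for reasons unrelated to the rehabilitation regime, sex and age among them. The Inclusion criteria admit men and women from 18 to 65. In an unadjusted comparison with 22 per arm, all of that variation stays in the error term. A baseline value would normally absorb part of it, but strength in the injured hand cannot be usefully measured before repair. The one functional item on the list does not help either, since eligibility makes active interphalangeal motion near zero in the affected digits of everyone enrolled.

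The uninjured hand is the natural stand-in for pre-injury strength, and allocation cannot affect it if it is measured at enrolment. An analysis plan can choose a model later, but it cannot adjust for a measurement that was never taken. The decision therefore belongs with data collection.

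**Working it through.** **Inputs from the Sample size calculations and Randomization sections.** Alpha is 0.05, two-sided because the printed formula uses z at alpha/2. Effect size is 0.3, with m = 4 visits, between-visit correlation 0.3, and 22 per group (N = 44).

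**Assumed.** r is the correlation of injured-hand strength with opposite-hand strength. The documents give none, so a range is shown. They also give no effect size for grip or pinch, so the primary outcome's standardised effect is borrowed.

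**1. Reproducing the plan's figure.** For the between-group test in a repeated measures ANOVA:

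λ = N f² m / [1 + (m − 1)ρ] = 44 × 0.09 × 4 / 1.9 = 8.34, with 1 and 42 degrees of freedom.

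Power is 0.805. N = 42 gives 0.786, so 44 is the smallest even total reaching 80%. The figure is reproduced when 0.3 is read as Cohen's f, which for two equal groups means d = 0.6. Entering 0.3 as δ in the printed formula, with between-group variance 0 and within-group variance 1, gives 83 per group instead. No covariate is needed to reach 44.

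**2. One visit, unadjusted.** With d = 0.6 and 22 per arm, the noncentrality is 0.6 × √(22/2) = 1.99 on 42 degrees of freedom. Power is 0.49.

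**3. One visit, adjusted for the opposite hand.** Residual variance is multiplied by 1 − r², the standardised difference becomes 0.6/√(1 − r²), and 41 degrees of freedom remain. The last column is 1/(1 − r²).

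| assumed r | variance removed | SE multiplied by | power | equivalent sample |
|---|---|---|---|---|
| 0.1 | 1% | 0.995 | 0.50 | ×1.01 |
| 0.3 | 9% | 0.954 | 0.53 | ×1.10 |
| 0.5 | 25% | 0.866 | 0.61 | ×1.33 |
| 0.7 | 49% | 0.714 | 0.78 | ×1.96 |

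**4. Mean of four visits.** This borrows the between-visit correlation of 0.3 and assumes the same r at each visit. Unadjusted variance is (1 + 3 × 0.3)/4 = 0.475 in units of the single-visit variance; adjusted variance is 0.475 − r².

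- r = 0.3: 0.385, a 19% reduction; power rises from 0.805 to 0.88.
- r = 0.5: 0.225, a 53% reduction; power 0.98.
- r = 0.7: not possible, since 0.49 exceeds 0.475. The top row of the range therefore applies to single visits only, unless strength is more highly correlated between visits than 0.3.

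**The case against.** The strongest reply is that the article states nothing wrong. It condenses a fuller protocol. It refers to a departmental proforma and an enrolment checklist that are not shown, and either may already record dominance or the opposite hand. Covariates are commonly left to the analysis plan. A randomised comparison is valid without a baseline, and its standard error already allows for chance imbalance. Age, gender and injury grade are collected, so some adjustment is possible as things stand. All of this is correct, and it limits the point to an improvement.

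Four stronger readings are tempting, and the documents do not support them:

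- *Strength and motion are compared as raw values.* The scale of grip and pinch is not stated, and motion is read through graded criteria for total active movement.
- *The trial has lost precision.* Nothing is lost against the plan's own calculation, which assumed no covariate and concerns the primary outcome. No power is claimed for grip or pinch.
- *The opposite hand would recover much of the variance.* That depends wholly on r. At 0.3 the single-visit gain is about four points of power; removing about half the variance at one visit needs r of about 0.7.
- *The same gain applies to total active movement.* An uninjured hand's motion should vary little between patients, so it would probably add almost nothing to the primary analysis. This is reasoning, not a figure from the documents.

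What survives is that the stated comparison is unadjusted, the listed functional item cannot act as a baseline, and the opposite-hand value has to be collected if it is to be used.

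**Conclusion.** The point holds as a low-cost gain in precision for two secondary outcomes. It is neither an error nor a bias, and it leaves the sample size and the primary analysis untouched.

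For r between 0.3 and 0.7, single-visit variance falls by 9% to 49%, and power for a 0.6 SD difference rises from 49% to between 53% and 78%. At r = 0.1 there is practically no gain. These figures rest on the assumed r, on borrowing d = 0.6 from the primary outcome, and on a linear relation with common variance in the two arms. If the unseen enrolment forms already record opposite-hand strength, only the analysis wording remains to be added.

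**What to change.** 1. At enrolment, measure grip and pinch once in the opposite hand with the instruments used at follow-up, and record hand dominance.
2. Pre-specify the opposite-hand value as a covariate for the same outcome (grip for grip, pinch for pinch), in an ANCOVA at a single visit or in the repeated-measures model.
3. Name sex and age, already collected, as further or fallback covariates. Keep the list short, since each covariate uses one of about 41 degrees of freedom.
4. State what happens when the opposite hand cannot be tested, for example a missing-value indicator so that the patient stays in the analysis. Bilateral injury is not explicitly excluded.
5. Results as a percentage of the opposite hand may be added descriptively. The covariate should carry the test: with equal SDs, subtracting the opposite-hand value multiplies variance by 2(1 − r), which is 1.4 at r = 0.3 and 1.0 at r = 0.5, whereas adjustment gives 0.91 and 0.75.

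Total active movement needs no such covariate. The cost is a few minutes per patient, a few fields on the proforma and one or two sentences in the analysis section. The downside is that a patient with an impaired opposite hand has no reference value. For patients already enrolled, a later opposite-hand measurement is a possible substitute, but it is no longer strictly a pre-treatment value and should be flagged as such.

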### Postoperative **care**

Patients in both groups will receive a dorsal thermoplastic splint on day five and start on either the active or passive mobilization program. Table 1 displays the protocol for mobilization.

### Safety **monitoring and adverse events reporting**

Adverse events will be documented and supervised by the principal investigator and promptly reported to the IEC within 24 h. In the event of a complication, treatment expenses will be covered by the investigating department and institution.

Benefits: After a hand therapy program is completed, the study will assist in determining the correlation between variables and their impact on the outcome of zone-5 flexor tendon restoration. Once established, corrective actions and rehabilitation can be used to further mitigate the impacts of variables and achieve a beneficial outcome in these injuries.

### Sample **size calculations**

At a 5% level of significance with 80% power and an effect size of 0.3, the minimum sample size (per group) required for a two-group repeated measures study design involving one primary quantitative outcome measured across four time points [six weeks, three months, six months, one year] (correlation among repeated measures is clinically presumed to be 0.3), was 44, i.e., 22 per group.

The sample size is computed using G*Power 3.1.9 and based on the formula mentioned below.

Formula.

$$n=\frac{2}{{{\delta ^2}}}\left[ {\mathop \sigma \nolimits_{b}^{2} +\frac{{{\sigma ^2}}}{k}\left[ {1+\left({k - 1} \right)\rho } \right]} \right]{\left({{z_{{\raise0.7ex\hbox{$\alpha $} \!\mathord{\left/ {\vphantom {\alpha 2}}\right.\kern-0pt}\!\lower0.7ex\hbox{$2$}}}}+{z_\beta }} \right)^2}$$

Where,

$$\mathop \sigma \nolimits_{b}^{2} $$: Between group variance

$${\sigma ^2}$$: Within group variance

$$\rho $$: Intra class correlation coefficient

$$\delta $$: Effect size

*K*: Number of repeated measures

$$\alpha $$: Significance level

$$1 - \beta $$: Power

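### The sample size of 44 does not follow from the formula printed for it: 0.3 works as Cohen's f (a 0.60 SD difference), not as the formula's delta, and 44 is mislabelled as a per-group figure

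*Protocol article*

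**What the plan says.** The section Sample size calculations opens with "At a 5% level of significance with 80% power and an effect size of 0.3, the minimum sample size (per group) required" for a two-group repeated-measures design with one quantitative primary outcome, "measured across four time points [six weeks, three months, six months, one year". The sentence ends with "correlation among repeated measures is clinically presumed to be 0.3), was 44, i.e., 22 per group".

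On the method it says: "The sample size is computed using G*Power 3.1.9 and based on the formula mentioned below". The formula is

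n = (2/delta²) × [sigma_b² + (sigma²/k) × (1 + (k − 1) × rho)] × (z_alpha/2 + z_beta)²

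Its legend defines delta as the effect size, sigma_b² as "Between group variance", sigma² as the within-group variance, rho as the intraclass correlation and K as the number of repeated measures. Neither variance is given a value. The text does not say whether 0.3 is Cohen's f or a standardised mean difference, and it does not name the G*Power test.

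Randomization and blinding states 44 patients, allocated 1:1 with 22 in each group. Statistical analysis plans a repeated-measures ANOVA over time and between groups.

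**The concern.** The section prints its inputs, a formula and a result, and the three do not agree. Taken at its word, the formula with delta = 0.3 asks for several times the stated number per group. In addition, one sentence presents 44 as the per-group minimum and then gives 22 per group.

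What is at stake is the size of effect to which the 80% applies. Anyone who follows the printed legend will take 0.3 as the standardised difference the trial can detect. If the calculation used Cohen's f, the detectable difference is twice that. A non-significant result would then be judged against a sensitivity that the trial does not have.

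**Working it through.** **Inputs.** From Sample size calculations: alpha 5%, two-sided because the formula uses z at alpha/2; power 80%; effect size 0.3; k = 4; rho = 0.3. From Randomization and blinding: 22 per group, 44 in total. Assumed because the article gives no values: sigma² = 1, so that delta is a standardised difference, and sigma_b² = 0, the most favourable choice for the plan.

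**1. Reproducing 44.** The between-factors test of a repeated-measures ANOVA has noncentrality lambda = f² × N × k / (1 + (k − 1) × rho), with 1 and N − 2 degrees of freedom. With f = 0.3:

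- N = 44: lambda = 0.09 × 44 × 4 / 1.9 = 8.34, power 80.5%
- N = 42: lambda = 0.09 × 42 × 4 / 1.9 = 7.96, power 78.6%

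So 44 is the smallest even total that reaches 80%. For two equal groups the standardised difference is 2f, so f = 0.30 is a 0.60 SD difference between arms, averaged over the four visits.

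**2. The printed formula at delta = 0.3.** The repeated-measures factor is (1 + 3 × 0.3)/4 = 1.9/4 = 0.475. The normal quantiles give (1.960 + 0.842)² = 7.849.

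- n = (2/0.09) × 0.475 × 7.849 = 82.8, so 83 per group (166 in total)

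A positive sigma_b² raises this:

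| sigma_b² (assumed, sigma² = 1) | n per group at delta = 0.3 |
|---|---|
| 0 | 83 |
| 0.3 | 136 |
| 0.5 | 171 |
| 1 | 258 |

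A one-sided 5% test would still need 66 per group.

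**3. The printed formula at delta = 0.6.** With sigma_b² = 0, n = (2/0.36) × 0.475 × 7.849 = 20.7, so 21 per group. This is close to 22; the formula uses normal quantiles and the F test does not. The formula and the stated size therefore roughly agree once delta is twice the printed value.

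**4. Power of 22 per group if 0.3 is a standardised difference.** Then f = 0.15 and lambda = 0.0225 × 44 × 4 / 1.9 = 2.08, which gives 29.2% power (30.3% by the normal approximation). Reading 44 as per group does not restore 80% either: at 0.3 SD it gives 52% (53% by the normal approximation).

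**5. Is the between-factors test the only source of 44?** No. The group-by-time interaction test with lambda = f² × N × k / (1 − rho) needs only 24 in total at f = 0.3. But if f is defined on the interaction's own error term, lambda = f² × (N − 2) × (k − 1) with 3 and 3(N − 2) degrees of freedom. At N = 44 that is 0.09 × 42 × 3 = 11.34, power 80.4%; N = 42 gives 78.1%. This version also returns 44, but it does not use rho.

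**The case against.** The best defence is that the sample size is not miscalculated. The article names G*Power, a two-group repeated-measures design, four visits and rho = 0.3, and the planned analysis is a repeated-measures ANOVA. For f = 0.30 the between-factors test returns exactly 44. On that view the defect is an unlabelled metric next to a generic formula that does not fit it. This stands, and it is why the remedy leaves 44 alone.

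It is also fair that 83 and 29% are conditional. The formula fixes no sample size until the variances are supplied: with sigma_b² = 0, a sigma² of about 0.27 (22/82.8) would return 22 per group, although nothing in the article suggests that value. The 29% applies only if 0.3 means 0.3 SD, which the article never says.

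A reader might infer that the trial is underpowered and needs 83 per group. The document does not support that: it gives no clinically required difference, and 44 fits f = 0.30. A reader might also infer that 44 can come only from the between-factors test. The second interaction calculation shows otherwise, though the stated rho favours the between-factors reading. Finally, the article plans no conclusion of equivalence, so a misread null result is a risk and not something the plan sets out to do.

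The defence does not remove the contradiction. The article itself says that the number is based on this formula and that delta is the effect size.

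**Conclusion.** The point holds as an inconsistency in the stated basis of the sample size, not as an error in 44 itself. With the printed effect size the printed formula gives 83 per group, against 22 stated, assuming sigma² = 1 and sigma_b² = 0. The stated 80% is right (80.5%) if 0.3 is Cohen's f in the between-factors test with rho = 0.3 and all 44 patients analysed; the difference then detectable is 0.60 SD. For 0.30 SD the power is about 29%. That f and this test were used is the likeliest reading, but it is an inference that the sponsor must confirm.

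The per-group label on 44 is wrong on any reading, because the allocation is 22 to each group. The correction matters because it changes the effect to which the trial's only power statement refers.

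**What to change.** - Keep 44 patients, and remove the bracketed per-group label so that 44 reads as the total.
- Have the sponsor confirm and state the effect-size metric and the G*Power test. If it was the between-factors test with f = 0.30, say that the 80% power is for a 0.60 SD difference between arms averaged over the four visits, with rho = 0.3 and all 44 analysed. If it was another test, state that test and its effect measure instead.
- Delete the formula, or enter the matching standardised difference. With delta = 0.6, sigma² = 1 and sigma_b² = 0 it gives 21 per group by normal approximation; say why this differs slightly from 22.
- Optional: one line on sensitivity. On the between-factors reading with f = 0.30, power is 69% at rho = 0.5 and 60% at rho = 0.7. At rho = 0.3 it is 77% with 40 patients analysed and 72% with 36. These alternative values are illustrations and do not come from the article.

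The cost is wording only, with no extra patients and no change to design or analysis. The stated detectable difference becomes less favourable than 0.3 suggests.
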